### 12.4 Interim monitoring and analyses

The first planned analysis of both trial arms will occur after a total of 60 patients have been recruited (30 patients in each arm). The research arm will be analysed to exclude any unexpected early toxicities, notably an excess of mucositis.

Interim analysis of the accumulating data will then be performed at regular intervals (annually) for review by the IDMC. These analyses will be performed by the WCTU. The IDMC will review the outcome Stage 1 is complete to endorse continuation into Stage 2.

The IDMC will review the results and, with consideration of any results from any relevant external trials, make a recommendation to the Trial Steering Committee (TSC) on whether the trial should continue recruitment or close to recruitment. While the trial is recruiting, only the appropriate staff at the WCTU and the IDMC will see the result of the interim analyses.

## **12.5 Statistical analyses**

All analyses will be on an intention-to-treat basis, i.e. all patients randomised will be included, and all patients will be analysed according to their allocated group whatever treatment they received.

A detailed statistical analysis plan will be prepared and finalised before analysis of the data.

The main analysis will compare overall survival between the two groups using a logrank test.

The secondary outcomes of proportions of patients with SAEs will be compared using a chi-squared test.

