## 6. TREATMENT REGIMEN AND SCHEDULES

### 6.1 Study treatments

Patients will be randomised to receive treatment on either of the following treatment arms.

Patients should start treatment within two weeks after randomisation.

Both arms will be delivered over 12 weeks.

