## 11. SAFETY REPORTING

The Medicines for Human Use (Clinical Trials) Regulations 2004 apply for this protocol:

**Adverse Event (AE):** any untoward medical occurrence in a subject to whom a medicinal product has been administered, including occurrences which are not necessarily caused by or related to that product.

**Adverse Reaction (AR):** any untoward and unintended response in a subject to an investigational medicinal product which is related to any dose administered to that subject.

**Serious Adverse Event (SAE):** Any adverse event that

- ◆ results in death
- ◆ is life-threatening\*
- ◆ requires hospitalisation or prolongation of existing hospitalisation\*\*
- ◆ results in persistent or significant disability or incapacity
- ◆ is a congenital anomaly or birth defect
- ◆ Other important medical events\*\*\*

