### 12.3 Sample size calculation

#### Stage 1:

The treatment failure-free rate in patients treated with CRT is approximately 60% at 24 weeks. With the addition of cetuximab it is felt that a treatment failure-free rate of less than 60% would not be sufficiently large enough to warrant further investigation in a Phase III setting, but that a rate of 75% or higher would warrant further investigation. Using a Fleming's single stage design,  $p_1=0.60$  and  $p_2=0.75$ , setting  $\alpha=0.05$  and 90% power 83 patients would be required. To allow for 10% not being assessable and with a 1:1 allocation 90 patients will be recruited into each arm, a total of 180 patients. The IDMC will review the treatment failure-free rate, along with toxicity and feasibility, before they endorse continuation into Stage 2.

#### Stage 2

Calculations were performed using the ART package in Stata 9 assuming a 3 year recruitment period followed by 1 year of follow up (based on a 2-sided log rank test). The 2 year overall survival rate in patients treated with CRT is approximately 35%. In order to detect an improvement in 2 year overall survival from 35% to 47.5% (Hazard Ratio [HR] =0.71) with 80% power at a 5% significance level a total of 420 patients (269 events) are required. A total of 210 patients will be recruited to each arm.

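### Intention-to-treat is fixed for every analysis, toxicity included, so randomised patients who never start treatment dilute the harm rates

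*Protocol*

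**What the plan says.** Protocol section 12.5 sets one population for everything: "All analyses will be on an intention-to-treat basis, i.e. all patients randomised will be included". Grouping is by allocation, regardless of what a patient was actually given. It makes no exception. A few lines later it applies this to harm: "The secondary outcomes of proportions of patients with SAEs will be compared using a chi-squared test".

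Section 11 defines an adverse event as "any untoward medical occurrence in a subject to whom a medicinal product has been administered". A serious adverse event begins from that same definition ("Any adverse event that") and so carries the same exposure condition.

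Section 6.1 leaves a gap between allocation and first dose: "Patients should start treatment within two weeks after randomisation". Section 1.2 describes the trial as open. Sections 10.9.1 and 13.1 keep patients who stop or change treatment in follow-up and analysis.

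Toxicity is a secondary outcome in both stages (section 12.2). It also informs the decision to go on: "The IDMC will review the treatment failure-free rate, along with toxicity and feasibility, before they endorse continuation into Stage 2" (section 12.3). Section 12.4 adds an early research-arm toxicity look after 30 patients have been recruited to each arm.

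**The concern.** Intention-to-treat protects the efficacy comparison because dilution there works against a claim of benefit. For harm, the same dilution works in favour of the new treatment: it lowers the observed rates and, if it is equal in both arms, narrows the difference between them. The protocol's population rule counts everyone randomised. Its event definition counts only people given a drug. Anyone who drops out between allocation and first dose falls between the two and appears in the table as a patient without toxicity.

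At stake are the rates that the data monitoring committee sees when it judges whether the research arm is safe enough to continue, and the final SAE comparison. In an open trial the share who never start could also differ between arms, and the distortion of the difference would then be unequal.

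This is not a detail left to a later analysis plan. Section 12.5 says that all analyses follow this rule, so a plan that made a treated set the basis of the toxicity comparison would depart from the protocol.

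**Working it through.** **Source of the denominator.** Section 12.3 gives 210 per arm ("A total of 210 patients will be recruited to each arm"). That figure reproduces. HR = ln(0.475)/ln(0.35) = 0.709. The Schoenfeld formula gives 266 events and the Freedman formula 271, against the stated 269. Exponential survival with 3 years of accrual and 1 year of follow-up gives 270 events from 420 patients. The sample size is not in dispute.

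**Inputs.**
- n = 210 per arm (section 12.3), two-sided 5%.
- Illustrative treated-patient rates: 34% v 18%, the grade 3-4 skin reactions in the head and neck trial described in section 2.4. This is the only between-arm toxicity contrast for cetuximab in the protocol. These are not SAE rates.
- d, the share of an arm that never starts: not stated in the protocol. Assumed 2%, 5% and 10%. The 10% in section 12.3 concerns Stage 1 patients who cannot be assessed and is not a non-start rate.

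**Formula.** If never-starters contribute no events, observed rate = treated-patient rate × (1 − d). The relative understatement is d. Power is from the usual normal approximation for two proportions.

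**Non-starting equal in both arms.**

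| d | Research | Control | Difference (points) | Power, n = 210 |
|---|---|---|---|---|
| 0 | 34.0% | 18.0% | 16.0 | 96.5% |
| 2% | 33.3% | 17.6% | 15.7 | 96.0% |
| 5% | 32.3% | 17.1% | 15.2 | 95.3% |
| 10% | 30.6% | 16.2% | 14.4 | 93.9% |

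For example, at 5%: 34 × 0.95 = 32.3, 18 × 0.95 = 17.1, difference 15.2.

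**Non-starting in the research arm only.**

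| d | Research | Control | Difference (points) | Power, n = 210 |
|---|---|---|---|---|
| 2% | 33.3% | 18.0% | 15.3 | 95.2% |
| 5% | 32.3% | 18.0% | 14.3 | 92.5% |
| 10% | 30.6% | 18.0% | 12.6 | 85.6% |

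If only the control arm lost starters, the gap would widen instead: 34 − 18 × 0.95 = 16.9 points at 5%. Each arm's own rate can only be understated, but the difference can move either way.

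**A higher-toxicity illustration.** Assume 65% v 50% in treated patients; neither is an SAE rate given in the protocol. At equal d = 5% the rates become 61.8% v 47.5%, and the gap falls from 15.0 to 14.3 points (65 × 0.95 − 50 × 0.95 = 14.25). Power falls from 87.8% to 83.7%. With 5% lost from the research arm only, the gap is 61.75 − 50 = 11.8 points and power is 68%.

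**How much of the power loss a treated set recovers.** At equal d = 5%, n falls to 210 × 0.95 = 199.5 per arm. Power in treated patients is then 95.7% (against 95.3%) for 34% v 18%, and 86.1% (against 83.7%) for 65% v 50%. The main gain is correct rates, not power.

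**The early look.** With 30 patients in the research arm, two non-starters multiply every rate by 28/30 = 0.933, a relative understatement of 7%.

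**The case against.** The strongest reply is that the effect is small and rests on unknowns. Nothing in the protocol says how many patients will fail to start. The two-week limit in section 6.1 bounds the gap and is not evidence of attrition, and section 4.1.1 requires consent and fitness for all protocol treatment before randomisation. At 2-5% equal non-starting the difference moves by less than one point. The protocol claims no power for the SAE comparison, so no stated operating characteristic is wrong. All of this stands, and it limits the size of the point.

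A reader might infer more than the text supports, in three ways.

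- *Never-starters are certain non-events.* This is too strong. Section 11 speaks of any medicinal product, not only protocol drugs, and section 13.1 lets the investigator give alternative treatment while the patient stays in follow-up. SAE reporting in section 11.1 also refers to time on trial, and toxicity is scored at baseline as well as during treatment (section 12.2). Some events in never-starters could therefore be recorded. It remains true that such patients have little chance of contributing toxicity from protocol treatment.
- *Research-arm patients who have chemoradiation without any cetuximab distort the safety data.* The schedule in section 6.2.2 infuses cetuximab before cisplatin on the first day, so this group should be rare.
- *The Stage 1 safety decision is compromised.* The protocol sets no numerical toxicity threshold for Stage 1, so nothing shows that a change of a few percent in a denominator would alter the committee's judgement.

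It can also be said that a supplementary table in treated patients is ordinary analysis-plan content. That is so, but section 12.5 as worded leaves the diluted version as the protocol's own comparison.

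**Conclusion.** The point holds in a limited form. The population rule in section 12.5 and the event definition in section 11 do not fit together, and no safety set reconciles them. Harm rates are understated by roughly the share who never start. The direction for each arm's rate is clear whenever that share is above zero; the size is not known from the protocol.

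Under the assumed 2-5% equal non-starting, the effect is small: 16.0 points becomes 15.7 to 15.2. It becomes material if non-starting is concentrated in one arm: with research-arm loss only, 14.3 points at 5% and 12.6 at 10%, and for the assumed 65% v 50% case power of 68% at 5%. It can also matter in the early look at 30 patients per arm. The figures rest on the assumed d, on illustrative toxicity rates that are not SAE rates, and on never-starters contributing essentially no events. The documents do not support a claim that toxicity will be seriously masked. They do support correcting a rule that errs towards understating harm and is cheap to change.

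**What to change.** In section 12.5, limit the intention-to-treat sentence to overall survival and the other efficacy and quality-of-life outcomes. Add that toxicity and SAEs are analysed in all patients who received at least one dose of protocol treatment, kept in their allocated arm. Use the same set for the Stage 1 and data monitoring committee toxicity tables, including the look at 30 per arm. Report the number who never started, by arm, and show the all-randomised toxicity table alongside.

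Do not make receipt of cetuximab the grouping for the main safety comparison. That would move research-arm patients who missed cetuximab, possibly because they had deteriorated, into the control group and could hide harm.

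The cost is a sentence or two and one extra table, with no change to sample size or treatment. The small downside is that the treated set is not strictly the randomised set; the all-randomised table and the count of never-starters let the reader judge that.

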### 4.3 Randomisation

Randomisation will be performed centrally by the WCTU. Patients will be randomised using the method of minimisation with an element of randomisation. Minimisation will ensure balanced treatment allocation by centre and a number of potential prognostic factors. Randomisation will use a 1:1 allocation ratio.

Randomisation can only be performed after the WCTU has confirmed that the patient is eligible, the patient has signed the consent form and completed a baseline Quality of Life (QoL) questionnaire. After baseline evaluation the Research Nurse or Doctor should complete the randomisation form and telephone the WCTU:

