## 12. STATISTICAL CONSIDERATIONS

### 12.1 Method of randomisation

Patients will be randomised centrally using the method of minimisation which includes a random element. Patients will be stratified for a number of clinically important stratification factors. The randomisation ratio for control:research arm will be 1:1.

The trial will be conducted in two stages.

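### The primary survival test is named only as a logrank test, with no stated account of the minimisation factors, so it may be conservative and forgo attainable power

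*Protocol*

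**What the plan says.** On allocation, protocol section 4.3 states: "Minimisation will ensure balanced treatment allocation by centre and a number of potential prognostic factors". Section 12.1 adds: "Patients will be stratified for a number of clinically important stratification factors". The method includes a random element and the ratio is 1:1. The factors are neither listed nor counted.

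On analysis, section 12.5 states: "The main analysis will compare overall survival between the two groups using a logrank test". Nothing there mentions stratification or covariates. The same section announces the SAP: "A detailed statistical analysis plan will be prepared and finalised before analysis of the data".

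On sizing, section 12.3 (Stage 2) takes 2-year survival of 35% against 47.5%, a hazard ratio of 0.71, over 3 years of recruitment and 1 year of follow-up. The calculation is "based on a 2-sided log rank test", and "with 80% power at a 5% significance level a total of 420 patients (269 events) are required".

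**The concern.** Minimisation forces the arms to be alike on the chosen factors. If those factors predict death, the treatment comparison varies less from trial to trial than it would under simple randomisation. The variance formula of the plain logrank test does not know this and still assumes the larger variation. The test statistic is then under-dispersed under the null, the true type I error is below the nominal 5%, and some of the precision bought by balancing goes unused. A logrank test stratified by the same factors restores the nominal level and recovers the precision.

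What is at stake is efficiency in the trial's one confirmatory survival comparison, which is planned at 80% power with 269 events. The factors are collected at randomisation in any case.

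**Working it through.** **1. Reproduce the plan's own figure.** Inputs are from section 12.3.

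- Hazard ratio: ln 0.475 / ln 0.35 = 0.709.
- Events (Schoenfeld): 4(1.96 + 0.84)² / (ln 0.709)² = 266. Events (Freedman): (1.96 + 0.84)² × [(1 + 0.709)/(1 − 0.709)]² = 271.
- Power at 269 events: Φ(√269 × |ln 0.709|/2 − 1.96) = 80.5% (Schoenfeld), or 79.7% (Freedman).
- With exponential survival, uniform accrual over 3 years and a cut at 4 years, the death probability is 0.702 in the control arm and 0.585 in the research arm, mean 0.643. Then 420 × 0.643 ≈ 270 events.

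The stated 269 events, 420 patients and 80% power are therefore correct for a plain two-sided logrank test.

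**2. Simulate that trial under minimisation.**

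- From the protocol: 420 patients, 1:1, 3 + 1 years, marginal 2-year survival held at 35% and 47.5%, minimisation with a random element on centre and other factors.
- Assumed, because the protocol does not give them: three binary factors at 50% prevalence, each with hazard ratio 1.0, 1.3, 1.5 or 2.0; 20 centres with no prognostic effect; probability 0.8 of the favoured arm.
- Holding the marginal rates fixed requires hazard ratios within factor levels of 0.709, 0.704, 0.696 and 0.670 respectively.
- Each of 6000 trials per scenario is tested by the plain logrank and by a logrank stratified on the three factors.

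| HR of each factor | Type I, plain | Type I, stratified | Power, plain | Power, stratified | Gain (points) |
|---|---|---|---|---|---|
| 1.0 | 4.6% | 4.8% | 81.6% | 80.1% | −1.5 |
| 1.3 | 5.3% | 5.7% | 79.9% | 80.1% | about 0 |
| 1.5 | 3.9% | 4.8% | 80.5% | 82.3% | +1.8 |
| 2.0 | 3.1% | 5.3% | 82.7% | 89.0% | +6.3 |

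Monte Carlo standard errors are √(0.05 × 0.95/6000) ≈ 0.3 points for type I error and √(0.8 × 0.2/6000) ≈ 0.5 points for power.

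**3. Check the mechanism.** Under the null with factor hazard ratios of 2.0, the plain statistic has standard deviation 0.907 and the stratified one 1.000. A normal statistic with standard deviation 0.907 exceeds 1.96 in absolute value with probability 2Φ(−1.96/0.907) ≈ 3.1%, as simulated. At 1.5 the standard deviation is 0.962, giving 2Φ(−1.96/0.962) ≈ 4.2%, against 3.9% simulated.

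**4. Repeat.** A further 3000 trials per scenario gave the following, plain against stratified:

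- Factor hazard ratio 1.5: type I error 3.1% and 4.1%; power 81.0% and 83.1% (+2.1).
- Factor hazard ratio 2.0: type I error 3.5% and 5.8%; power 81.5% and 87.9% (+6.4).
- Factor hazard ratio 1.3: no material difference.

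**The case against.** The strongest reply is that section 12.5 does not say the test is unadjusted. A stratified logrank is also a logrank test, and the sentence before it hands the detail to an SAP that is not at hand and may well stratify. The plan is also coherent as it stands: section 12.3 sizes the trial on marginal survival rates with the same kind of test, and that test delivers the planned power. Any error is in the safe direction.

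Most of this stands, and it sets the size of the point. It does not remove it. The protocol itself names the primary test, the only version its sizing shows is the plain one, and a better use of the allocation factors is available at almost no cost.

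Three stronger readings are tempting and are not supported:

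- **The trial is underpowered.** A reader might infer this by taking 0.709 as the hazard ratio within factor levels. Simulated that way (4000 trials per scenario), plain against stratified power is 75.1% and 77.2% at factor hazard ratio 1.5, and 69.7% and 78.5% at 2.0. But section 12.3 derives 0.71 from overall survival rates, which makes it a marginal effect. On that footing power is 80-83%.
- **The plain hazard ratio is biased towards 1.** The marginal and conditional hazard ratios are different quantities. The gap between them is not an error in the plan.
- **Section 14 contradicts section 12.5** because the quality-of-life model is to take account of prognostic factors. A fuller sub-study plan beside a brief main one is not a contradiction.

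**Conclusion.** The point holds as a conditional, minor efficiency point. The protocol balances on potentially prognostic factors and states no use of them in the primary test. If they are moderately to strongly prognostic, the plain logrank runs at about 3-4% instead of 5% and forgoes about 2 points of power (three factors of hazard ratio 1.5) to about 6 points (three of 2.0). At 1.3 or below nothing material is lost.

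The planned 80% on the section 12.3 rates is retained and type I error is not inflated. The direction follows from the allocation method. The size rests on assumed number, prevalence and strength of factors that the protocol does not name, so it cannot be fixed from the document. Centre was given no prognostic effect, so these figures say nothing about gains or losses from adjusting for centre.

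**What to change.** In section 12.5, state that the primary test of overall survival is a two-sided logrank test stratified by the main minimisation factors as recorded at randomisation, with centre left out of the strata, and that the unstratified logrank is a supportive analysis. Name the factors before any outcome data are examined. Keep them few: three binary factors give 8 strata of about 420/8 ≈ 52 patients and 269/8 ≈ 34 deaths each, and more factors would thin the strata quickly.

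The cost is one sentence, with no extra patients or data. There are two downsides. If the factors turn out not to be prognostic, stratifying costs about 1-2 points of power (81.6% to 80.1% in the simulation). The hazard ratio that goes with the stratified test is conditional on the strata, whereas section 12.3 plans on the marginal contrast, so the unstratified estimate should be reported alongside it.

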## **12.6 Subgroup analyses**

No formal subgroup analyses are planned. However, if any treatment difference is found we will look to see whether it is consistent across patient subgroups (defined by all pre-treatment factors collected) although this analysis will be exploratory in nature.

## **13. INFORMED CONSENT, ETHICAL & REGULATORY CONSIDERATIONS**

### **13.1 Ethical and other issues**

The protocol will have the favourable opinion of a Multi-centre Research Ethics Committee (MREC) but a REC must also approve each centre, through the SSI process, before patients are recruited at that centre. All patients must be informed of the aims of the study, the known possible adverse events, the procedures and possible hazards to which they may be exposed. They will be informed of the strict confidentiality of their data, but that their medical records may be reviewed for trial purposes by authorised individuals other than their treating physician.

The patient's consent to participate in the trial should be obtained after a full explanation has been given of the treatment options, including the conventional and generally accepted methods of treatment. The patient's consent will also be sought to notify their GP of their involvement in the trial. Patients should be given sufficient time after being given the trial Patient Information Sheet, to consider and discuss participation in the trial with friends and family. A contact number should be given to the patient should they wish to discuss any aspect of the trial. Following this, the randomising investigator should determine that the patient is fully informed of the trial and their participation is in accordance with UK regulations. Patients should always be asked to sign and date a consent form. One copy should be given to the patient but the original copy should be kept in the study site file and a further copy should be kept with patient's hospital notes.

The right of the patient to refuse to participate in the trial without giving reasons must be respected. After the patient has entered the trial, the investigator must remain free to give alternative treatment to that specified in the protocol, at any stage, if he/she feels it to be in the best interest of the patient. However, the reason for doing so should be recorded and the patient will remain within the trial for the purpose of follow-up and data analysis according to the treatment option to which he/she has been allocated. Similarly, the patient must remain free to withdraw at any time from the protocol treatment without giving reasons and without prejudicing his/her further treatment.

This is a randomised controlled trial therefore neither the patients nor their physicians will be able to choose the patient's treatment. Treatment will be allocated randomly using a computer-based algorithm. This is to ensure that the groups of patients receiving each of the different treatments are similar.

